## Methods and analysis

### Study design

Single centre two-armed randomised controlled trial. Patients will be randomised (1:1) to UC or SR plus UC.

### Sample size

We aim to recruit 36 patients. The sample size was estimated using a one-tailed two independent sample t-test with a standardised effect size of 0.93 (estimated using a previous publication in a similar population using the same assessment methodology)^40^ with an alpha of .05 and power of .80 producing a sample size of 30 to detect a difference in AF symptom score. A 20% drop-out rate has been factored in to give a total sample size of 36 randomised 1:1.

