### Data analysis

The distributional properties of the continuous variables will be examined by plots. Participant baseline characteristics and health outcomes will be summarised (including missing data) using descriptive measures: mean (SD) or median (IQR) for symmetric or skewed continuous variables, respectively; number (percent) for categorical variables; and mean (SD) absolute and percent change for longitudinal data will be reported separately by treatment allocation.

The primary outcome, change in AF symptom score, will be assessed using a two-way analysis of covariance (ANCOVA) adjusted for baseline score and AF type using data from subjects where both baseline and follow-up data are complete. The impact of missing follow-up data on the primary analysis will be explored with sensitivity analysis using methods such as last observation carried forward. This approach is likely to provide a conservative estimate of treatment effects. A prespecified secondary analysis will include a two-way ANCOVA for change in AF symptom score at 6 months, again adjusted for baseline score and AF subtype. To aid interpretation, changes will be considered in light of the minimally clinically important difference (MCID). While an anchor-based MCID has not yet been formally established for the AFSS, changes of approximately 3–5 points are considered clinically meaningful in analogous AF-specific instruments, such as the AFEQT. This range will be used to contextualise the clinical relevance of observed changes.

For continuous secondary outcomes, two independent samples t-tests or non-parametric alternatives will be used. Parametric assumptions will be checked by reviewing univariate histograms prior to formal analysis. For categorical secondary outcomes, change in status at follow-up will be compared between groups using χ² or Fisher’s exact test. Time to AF recurrence and event-free survival curves will be with Kaplan-Meier assessment and differences between curves tested with the log-rank test.

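### The sample size figures 30, 20% and 36 do not agree: 36 randomised with 20% drop-out leaves about 29 completers, slightly short of the 30 required

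*Protocol article*

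**What the plan says.** The Sample size section of the protocol article sets out the calculation in full. The recruitment target is given first: "We aim to recruit 36 patients". The method is then described: "The sample size was estimated using a one-tailed two independent sample t-test", "with a standardised effect size of 0.93", "with an alpha of .05 and power of .80", "producing a sample size of 30 to detect a difference in AF symptom score". The drop-out allowance follows: "A 20% drop-out rate has been factored in to give a total sample size of 36 randomised 1:1". The formula used for the allowance is not given.

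The Data analysis section specifies an ANCOVA for the primary outcome, adjusted for baseline score and AF type, "using data from subjects where both baseline and follow-up data are complete". Last observation carried forward appears only as an example of a sensitivity analysis for missing follow-up data.

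**The concern.** A drop-out rate is the share of those randomised who are lost. Read that way, 20% of 36 is 7.2, and the remaining 28.8 is below the 30 that the same paragraph says is needed. The three figures cannot all hold.

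The mismatch reaches the primary analysis because that analysis has no imputation. A participant without 12-month symptom data drops out of it, and the number analysed falls one for one. The stated power of 80% is therefore not met at the stated drop-out rate, and anyone repeating the sentence in the results paper would claim a tolerance for loss that the design does not have.

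**Working it through.** **Inputs**, all from the protocol article:

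- Two-sample t-test, one-tailed, alpha 0.05, power 0.80, d = 0.93, required total 30, drop-out 20%, randomised total 36 (Sample size).
- Allocation 1:1 (Study design).
- Complete-case primary analysis (Data analysis).

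**Step 1. Reproduce the 30.** The normal approximation per arm is 2(z₀.₉₅ + z₀.₈₀)²/d² = 2 × (2.4865)²/0.93² = 14.30, rounded up to 15, or 30 in total. This matches the article. The exact noncentral t distribution gives power 0.7995 at 15 + 15. Strictly reaching 0.80 would take 16 + 16 (power 0.823), so 30 is a fair rounding but leaves no slack.

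**Step 2. Apply 20% drop-out to 36.** 36 × (1 − 0.20) = 28.8 expected completers, 1.2 fewer than 30.

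**Step 3. Work back from 30.** 30/(1 − 0.20) = 37.5, so 38 randomised (19 per arm). The stated total is 2 lower.

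**Step 4. Find the loss that 36 does cover.** 1 − 30/36 = 16.7%, or 6 participants.

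**Step 5. See where 36 could come from.** 30 × 1.20 = 36 exactly. This suggests that the allowance was multiplied on, but does not prove it.

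**Step 6. Cost in power.** For the unadjusted one-tailed t-test at d = 0.93, the noncentrality is d√(n₁n₂/(n₁+n₂)) with n₁ + n₂ − 2 degrees of freedom:

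| Completers | Noncentrality | One-tailed power |
|---|---|---|
| 15 + 15 | 2.547 | 0.7995 |
| 14 + 15 | 2.503 | 0.786 |
| 14.4 + 14.4 (expectation) | 2.495 | 0.784 |
| 14 + 14 | 2.461 | 0.774 |

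The expected loss is 0.7995 − 0.784 = 0.015, about 1.5 percentage points. It is 1.3 points with 29 completers and 2.6 with 28.

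**Step 7. Chance of ending below 30.** This assumes that each participant is lost independently with probability 0.20, which the article does not state. The binomial probability of fewer than 30 completers is then about 60% with 36 randomised and about 34% with 38.

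**The case against.** The case for leaving the sentence alone has three parts.

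*The route to 36 is unknown.* The unrounded normal-approximation total is 2 × 14.30 = 28.59, and 28.59/0.80 = 35.7, which rounds to 36. On that route the allowance was divided in properly. This stands as a reason not to assert that 30 was multiplied by 1.2. It does not reconcile the printed figures: the article gives 30 as the requirement, and 36 with 20% loss yields fewer than 30 by any route. It also names a t-test, under which 28.59 is too few for 80% power.

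*The ANCOVA may recover the loss.* Suppose that 0.93 is the effect on the unadjusted follow-up scale. With 14 + 14 completers and two degrees of freedom spent on covariates, one-tailed power is then 0.772, 0.787, 0.805 and 0.868 at baseline–outcome correlations of 0, 0.2, 0.3 and 0.5. A correlation of about 0.3 would make up the shortfall. The article gives neither the correlation nor the scale on which 0.93 was derived, and its calculation claims no such gain. This is a possible offset to actual power, not a correction of the stated figures.

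*The effect is trivial beside the uncertainty in 0.93,* which rests on one earlier publication. This is a fair point and it limits the weight of the finding. It does not make the sentence right.

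There is also a stronger reading to resist. A reader might compute two-sided power at 28 or 29 completers (0.659 or 0.675) and conclude that the drop-out allowance leaves the trial badly underpowered. The documents do not support that. The calculation is explicitly one-tailed, and two-sided power is already 0.691 with the full 15 + 15. Nearly all of that gap comes from the choice of sidedness, which is a separate question.

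**Conclusion.** The inconsistency is real and follows from the article's own figures: 36 randomised does not retain 30 after a 20% loss, and 38 would be needed. The shortfall is 2 randomised participants, or 1.2 expected completers. One-tailed power is about 78% (77–79% across 28 to 29 completers), against just under 80% at 30.

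The completer counts need only the usual meaning of drop-out and the complete-case rule. The power figures also assume an unadjusted t-test, d = 0.93 and near-equal losses in the two arms. That the allowance was multiplied on is an inference from the match with 30 × 1.2. The finding calls for correcting a stated figure. It gives no ground for saying that the trial is materially underpowered or that its analysis is compromised.

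**What to change.** The Study status section reports that recruitment is complete, so the text should change, not the enrolment. Replace the drop-out sentence with:

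> 36 randomised allows for 16.7% drop-out (6 participants) to retain 30 evaluable; with 20% drop-out about 29 (28–29) are evaluable and one-tailed power is about 78% (77–79%).

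Keep two-sided power out of this sentence, so that the small drop-out effect is not confused with the effect of sidedness.

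The cost is one sentence and a slightly less favourable stated power. The design, data collection and analysis are unaffected. With follow-up still under way at submission, the correction can be made before the 20% figure is carried into the results paper, where the achieved number of completers should be reported beside it.

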### Study population and setting

Consecutive patients aged ≥18 years with either paroxysmal AF or persistent AF (defined as AF <1 year in duration at the time of referral to secondary care) will be prospectively identified at the Royal United Hospitals (RUH) Bath NHS Foundation Trust, a 750-bed district general hospital. Regional data demonstrated that over half (56%) of the local population are overweight/obese, with incidence rising in all communities.^41^ The RUH is aligned with current NICE guidance regarding the management of AF.^9^

### Patient identification and screening

Initial prescreening will prospectively identify patients referred for an ablation and/or DCCV through routine clinical care. Potential participants will be informed of the study protocol in writing and invited for an appointment at the study site. A clinician will then complete a face-to-face appointment where screening will be completed based on the inclusion and exclusion criteria outlined below.

### Inclusion criteria

Symptomatic paroxysmal or persistent AF.Aged ≥18 years.Patient has been referred for AF CA and/or DCCV as a result of routine clinical care.BMI ≥27 kg/m^2^

### Exclusion criteria

Participants will not be eligible if they have conditions that preclude high-intensity exercise, including:

Significant coronary artery disease, defined as left main stem >50% stenosis and/or ≥moderate stenosis in ≥3 major epicardial vessels requiring revascularisation.Unstable angina.Heart failure with severe left ventricular systolic dysfunction (ejection fraction ≤35%) and/or New York Heart Association Class III/IV heart failure symptoms.Significant cardiomyopathy (as assessed by a cardiologist).Severe valvular heart disease.Severe hypertension (BP >180/120 mmHg) despite anti-hypertensive treatment.Uncontrolled arrhythmia or higher degree of heart block.History of aortic dissection.Recent acute pulmonary embolus, deep vein thrombosis, stroke or transient ischaemic event (<6 months).Severe autonomic or peripheral neuropathy.Significant acute or chronic renal failure that would preclude contrast use at CT.Significant pulmonary fibrosis or interstitial lung disease (as assessed by a respiratory physician).Physical inability to participate in high-intensity exercise.Pregnancy or breastfeeding (due to the additional use of CT).Prior AF ablation.A clinically significant ECG abnormality, including but not limited to: sustained ventricular tachycardia, high-grade atrioventricular block (second-degree Mobitz type II or third-degree heart block), evidence of acute ischaemia (ST-segment elevation or depression >1 mm) or other arrhythmias deemed clinically significant by the study cardiologist.Participation in another rehabilitation research study.Inability to fully understand the instructions provided to them during the study.

Potential participants meeting the above criteria who are interested in joining the study will then be asked to provide informed consent for involvement in the trial. A copy of the consent form has been included in the supplementary material.

### Baseline assessments

Following consent to participate in the study, the following baseline data will be obtained (figure 1):

Medical history including medication listAnthropometrics including: height, weight, BMI, abdominal waist and hip circumferenceHbA1cSeven-day photographic diet diarySeven-day blood pressure diary (each patient will be supplied with a home blood pressure monitor).Seven day free living activity and energy expenditure: GeneActiv monitoring deviceBody composition: dual-energy X-ray absorptiometry (DEXA).AF symptom burden: AFSS questionnaire and EHRA scaleImpact on quality of life: EQ-5D-5L and AFEQTPsychological well-being assessment: HADS, ICECAP-ANHS resource-use questionnaire

**Figure 1 F1:**
[figure not shown]
Study assessment and intervention timeline. Baseline, 6-month, 12-month and 15-month assessments include questionnaires, blood tests, echocardiogram, CPET, DEXA, 7-day photographic food diary, BP diary and GeneActiv monitoring. CTCA is carried out at baseline and 12 months. ICM is inserted at baseline and extracted at 15 months. Abbreviations: BP, blood pressure; CPET, cardiopulmonary exercise test; CTCA, CT coronary angiography; DEXA, dual-energy X-ray absorptiometry; ICM, implantable cardiac monitor; SR, Super Rehab.

All consented participants will also have a baseline (1) transthoracic echocardiogram (TTE) assessing cardiac structure and function, (2) a CT coronary angiogram (CTCA) assessing both the coronary arteries and peri-atrial fat.^42^ Any severe valvular abnormalities and/or significant coronary artery disease diagnosed through these tests may preclude the participant from further involvement in the study, as outlined above.

In addition, a supervised symptom-limited cardiopulmonary exercise test (CPET) will be carried out to measure baseline level of fitness and to establish the ability of consented participants to complete high-intensity exercise safely. The results will also help to guide the prescription of exercise intensity parameters for those randomised to the intervention. Participants unable to complete the CPET will discontinue involvement in the study on safety grounds.

The CPET will be conducted on a cycle ergometer, beginning with a 5-minute warm-up against zero resistance. A subsequent ramp progression is used with resistance increasing by 5–25 watts per minute (individualised to participant). The test discontinues at volitional exhaustion targeting a Borg rating of perceived exertion (RPE) of ≥17. A subsequent recovery phase lasts ≥3 min against zero resistance. Achievement of VO_2_ peak will be assumed if the following criteria are met:^43^

1. Respiratory exchange ratio ≥1.10,

*or*

2. Increment in VO _2_≤5 mL/kg^-1^.min^-1^ in response to increasing gradient.

*and*

3. RPE ≥17.

On successful completion of the baseline assessments, all participants will have an ICM inserted subcutaneously to monitor AF burden for the duration of the study (Biomonitor IIIm, Biotronik SE and Co. KG). Although ICM implantation is invasive, the procedure is low risk, and participants will be closely monitored throughout the study to minimise any potential complications. ICM has been used in numerous AF studies, and they represent the gold standard of rhythm monitoring. Additional informed consent will be obtained for the implantation procedure. The device will be removed on completion of the study.

### Randomisation

Participants will then be randomised to either UC or SR using a web-based platform (Sealed Envelope: https://www.sealedenvelope.com/) in permuted blocks of four using an allocation sequence generated at random. Stratification will be by AF subtype (paroxysmal or persistent). Participants’ general practitioners will be informed of their patients’ involvement in the study and will be provided with a study information sheet.

### Intervention and control groups

#### Usual National Health Service (NHS care/control arm

In addition to any management advice given to patients through their routine clinical care, all participants in the study will be given one-off lifestyle advice by a clinician within the research team recommending moderate intensity exercise, weight loss and reduction in alcohol intake in line with ESC guidance.^10^

#### Super Rehab (plus usual care)/intervention arm

A detailed description of the SR protocol is provided in the online supplemental file 1. In brief, SR consists of a 52-week rehabilitation intervention targeting positive dietary changes, weight loss and improved physical fitness in addition to identifying and treating any modifiable AF risk factors. The SR programme is overseen and coordinated by a cardiologist with concurrent multidisciplinary expertise offered by a dietitian, PT and an arrhythmia specialist nurse practitioner provided in a 1:1 manner. Care is individualised with the aim of optimising the management of each participant’s AF. SR is divided up into three phases (1) *induction* (10 weeks), (2) *developing* (14 weeks) and (3) *maintaining* (28 weeks) with a graded reduction in the frequency of supervised sessions facilitating increased participant confidence and autonomy (see figure 2).

**Figure 2 F2:**
[figure not shown]
The Super Rehab programme.

*Dietetics*
Once randomised to the intervention arm, participants will receive a SR introductory educational booklet which includes the aims of SR in addition to structured dietary and exercise advice. A dietitian will work with participants using photographic diet diaries to identify areas for improvement. They will provide tailored advice through the study to identify and remove any residual barriers to dietary improvements. Dietitian sessions will take place either face-to-face or remotely depending on participant preference.ExerciseParticipants will undertake both supervised (with a PT) and homework-based exercise sessions. PT supervised sessions will consist of resistance training and high-intensity interval training using the Norwegian 4×4 model.^44^ Baseline CPET results for each participant will help provide guidance to set exercise intensity parameters. The PT will additionally prepare suggested homework exercises. PT-led sessions will be undertaken at a local gym facility.AF and risk factorsA 3-monthly clinical review delivered by an arrhythmia specialist nurse will aim to improve cardiospecific AF risk factors including lipid targets, glycaemic control and blood pressure control. SDB will be screened for and referred for further review as necessary. AF rhythm control strategy will be reviewed and heart rate controlled in line with guidance. Clinical review sessions will take place remotely.

### Assessments

In addition to baseline measurements detailed above, the following assessments will be carried out at 6, 12 and 15 months (see figure 1).

Medication listAnthropometricsFasting blood tests.Seven-day photographic diet diary.Seven-day blood pressure diarySeven-day free living activity.AFSS questionnaire and EHRA classEQ-5D-5L, AFEQT, HADS, ICECAP-A and NHS resource use questionnaires.TTEDEXACPETA repeat CTCA with peri-atrial fat analysis will be carried out at 12 months only.

### Study status

Recruitment for the study began on 3/4/23. At the time of manuscript submission, recruitment has been completed with follow-up and participant involvement still ongoing. The study is expected to complete final data collection by November 2025.

### Data management and data analysis plan

#### Data management

All data will be stored and analysed pseudonymously using a unique identifier code. An electronic cross-referencing list will be stored on an NHS password-protected computer database at the study site. Only pseudonymised data using the unique identifier code will be used on datasets shared with external collaborators. All research records will be destroyed after 10 years.

Peri-atrial assessment by CTCA used in this study requires images to be transferred off-site to the Oxford Translational Cardiovascular Research Group core lab at the University of Oxford. We will use the existing pathway for pseudonymised image transfer via the study sponsor’s collaboration with the University of Oxford on The Oxford Risk Factors And Non-Invasive Imaging Study,^45^ which has separately been approved by the South Central - Oxford C - Research Ethics Committee (Reference 15/SC/0545). Existing secure information sharing protocols for standard clinically indicated scans will be used for image transfer.

### Data analysis

The distributional properties of the continuous variables will be examined by plots. Participant baseline characteristics and health outcomes will be summarised (including missing data) using descriptive measures: mean (SD) or median (IQR) for symmetric or skewed continuous variables, respectively; number (percent) for categorical variables; and mean (SD) absolute and percent change for longitudinal data will be reported separately by treatment allocation.

The primary outcome, change in AF symptom score, will be assessed using a two-way analysis of covariance (ANCOVA) adjusted for baseline score and AF type using data from subjects where both baseline and follow-up data are complete. The impact of missing follow-up data on the primary analysis will be explored with sensitivity analysis using methods such as last observation carried forward. This approach is likely to provide a conservative estimate of treatment effects. A prespecified secondary analysis will include a two-way ANCOVA for change in AF symptom score at 6 months, again adjusted for baseline score and AF subtype. To aid interpretation, changes will be considered in light of the minimally clinically important difference (MCID). While an anchor-based MCID has not yet been formally established for the AFSS, changes of approximately 3–5 points are considered clinically meaningful in analogous AF-specific instruments, such as the AFEQT. This range will be used to contextualise the clinical relevance of observed changes.

For continuous secondary outcomes, two independent samples t-tests or non-parametric alternatives will be used. Parametric assumptions will be checked by reviewing univariate histograms prior to formal analysis. For categorical secondary outcomes, change in status at follow-up will be compared between groups using χ² or Fisher’s exact test. Time to AF recurrence and event-free survival curves will be with Kaplan-Meier assessment and differences between curves tested with the log-rank test.

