### Primary objectives

1. To assess the difference in AF symptom burden (score range 0–35), as defined by the University of Toronto AF severity scale (AFSS), between usual NHS usual care (UC) and SR groups at 12 months. Additional evaluations will be conducted and reported at the 6- and 15-month time points.

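### The 12-month primary analysis leaves out collected 6-month AFSS scores, and its only named missing-data check, LOCF, is called conservative although its bias can go either way

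*Protocol article*

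**What the plan says.** The primary objective compares the AFSS symptom score (0–35) between arms at 12 months. Under Data analysis the model is a "two-way analysis of covariance (ANCOVA) adjusted for baseline score and AF type", fitted "using data from subjects where both baseline and follow-up data are complete". For a 12-month endpoint, that excludes anyone without a 12-month score.

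Missing follow-up is to be explored in a sensitivity analysis with "methods such as last observation carried forward. This approach is likely to provide a conservative estimate of treatment effects". No condition or reason is attached to the statement about conservatism.

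Under Assessments, "the following assessments will be carried out at 6, 12 and 15 months", and the AFSS is on that list. The 6-month score has its own separate ANCOVA but does not enter the 12-month model.

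The Sample size section allows for 20% drop-out. It does not say when the losses occur or how they divide between the arms.

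**The concern.** Two choices combine on the primary endpoint.

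- **Unused information.** Someone who completes month 6 and then leaves contributes nothing to the 12-month comparison, although the 6-month score is probably the best available predictor of the missing one. If leaving is related to that score, for example because participants doing poorly on Super Rehab (SR) give up the programme, those who remain are a selected group.
- **A check with a presumed direction.** LOCF is introduced as erring against the treatment. A reader would then take agreement between LOCF and the primary result as reassurance. That is warranted only if the direction of LOCF bias is known, and it depends on how scores move over time and on who leaves when.

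At the planned rate, about 36 × 0.20 = 7 participants are affected. In a trial of this size, how they are handled matters.

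**Working it through.** **Inputs from the protocol:** 36 participants, 18 per arm; 20% drop-out; standardised effect 0.93 (Sample size); AFSS at baseline, 6, 12 and 15 months.

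**Assumed, because the protocol does not give them:** trajectories, timing of loss, loss by arm, and correlations between visits. Effects are in SD units; positive favours SR.

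**1. LOCF when loss is unrelated to the score within an arm.** With the same loss in both arms, the expected LOCF difference is

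(share observed at 12 months) × (12-month effect) + (share lost after month 6) × (6-month effect) + (share lost before month 6) × 0.

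The last term is zero because baseline is carried forward and the arms are equal at baseline.

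| Assumed pattern, 20% lost per arm | Truth at 12 months | LOCF |
|---|---|---|
| 0.93 at month 6 waning to 0.50; all lost after month 6 | 0.50 | 0.8×0.50 + 0.2×0.93 = 0.59 |
| Same, half lost before and half after month 6 | 0.50 | 0.8×0.50 + 0.1×0.93 = 0.49 |
| 0.93 at month 6 fully waned; all lost after month 6 | 0 | 0.2×0.93 = 0.19 |
| Same, half before and half after | 0 | 0.1×0.93 = 0.09 |
| Effect appears only after month 6; all lost after month 6 | 0.93 | 0.8×0.93 = 0.74 |
| 0.93 from month 6 onward; half before and half after | 0.93 | 0.8×0.93 + 0.1×0.93 = 0.84 |

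**2. LOCF with unequal loss and no treatment effect.** Suppose both arms improve by 0.93 after month 6, for instance after a procedure. The bias towards SR is (usual-care (UC) loss − SR loss) × 0.93:

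- UC 30%, SR 10%: 0.20 × 0.93 = +0.19, towards SR.
- 20% in each arm: 0.
- UC 10%, SR 30%: −0.20 × 0.93 = −0.19, against SR.

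Simulation of the planned ANCOVA (18 per arm, visit correlations 0.5, 0.5 and 0.7) agreed with the cases it covered: LOCF gave 0.18–0.19 in the fully waned case and 0.74 in the late-emerging case.

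**3. Complete-case bias when loss depends on the 6-month score.** Same simulation, with no true effect. SR participants with poor 6-month scores are more likely to leave (logistic slope 1.5 per SD, 20% loss at an average score); UC loss is 20% at random.

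| Estimator | Mean (truth 0) |
|---|---|
| Complete-case ANCOVA | 0.14 towards SR |
| LOCF | 0.06 against SR |
| Regression estimate using the 6-month score | 0.00 |

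In this setting average SR loss is about 27%. On re-running with SR loss set to about 21%, the complete-case bias was 0.11. Variants with other loss rates by arm, including good responders leaving UC, gave 0.09–0.18. With a true effect of 0.93 under the first setting, complete-case gave 1.06, LOCF 0.86 and the estimate using the 6-month score 0.93.

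**The case against.** The case for leaving the plan alone has real force.

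- **The wording is hedged.** The protocol says "likely" and "methods such as", so LOCF is neither the only permitted method nor guaranteed to be conservative. Full imputation detail commonly sits in a SAP, which is not shown. This stands as to detail. It does not supply a reason for the stated direction.
- **LOCF sometimes is conservative.** It shrinks a sustained or late-emerging effect, and it erred against SR in the scenario that biased the complete-case estimate towards SR. This stands, and is why the finding is that the direction is undetermined.
- **Complete-case ANCOVA can be valid.** It is unbiased if loss depends only on arm, baseline and AF type. Where loss was random within arm, its simulated one-sided error stayed near the nominal 5% (4.8–5.1%). The biases of 0.1–0.2 SD compare with a sampling SD of about 0.3. This stands.
- **The 6-month score helps only some.** Participants lost before month 6 do not have one. This stands.

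A reader might go further and infer that LOCF will manufacture an effect for SR. The protocol does not support that. It describes a programme "with a graded reduction in the frequency of supervised sessions facilitating increased participant confidence and autonomy", but nowhere says that symptom benefit peaks at month 6 or wanes. Both arms are referred for ablation and/or DCCV, so pre-procedure scores can be carried forward in either. If the more demanding arm loses more people, that mechanism works against SR.

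Nor should the raised false-positive rates seen for LOCF in chosen scenarios (about 14% against a one-sided 5%) be read as the error of the primary test. They belong to the sensitivity analysis.

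**Conclusion.** The concern holds in a limited form, as something that should be fixed rather than as a flaw that invalidates the trial. The 12-month model discards relevant scores that are collected, and the statement that LOCF is likely conservative has no support in the document.

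In the assumed patterns LOCF ranges from overstating (0.50 to 0.59, or 0 to 0.19 SD) to understating (0.93 to 0.74–0.84 SD). Complete-case bias is about 0.1–0.2 SD if loss follows the 6-month response, and zero if loss depends only on arm, baseline and AF type. Every one of these sizes rests on assumed trajectories, timing, arm-specific loss and correlations. The protocol fixes only the overall 20%.

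**What to change.** Make the change before between-group results are seen; follow-up was still under way when the article was submitted.

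1. Delete the sentence calling the approach conservative.
2. Estimate the 12-month contrast with a method that uses the 6-month score. One option is a likelihood-based repeated-measures model with baseline score and AF type and a small-sample degrees-of-freedom correction such as Kenward–Roger. The other is multiple imputation that includes the 6-month score. The repeated-measures model can also serve the 6- and 15-month evaluations promised in the primary objective.
3. Replace LOCF with a delta-adjusted (tipping-point) or control-based sensitivity analysis, so that the departure being tested is stated openly.
4. Keep the complete-case ANCOVA as a supportive analysis.

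The cost is slightly more programming and the small-sample correction, with no new data or participants. Participants with no post-baseline score gain nothing from the repeated-measures model. The precision gain is small (an SD about 1–4% smaller in simulation), so the main benefit is protection against bias.
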